**Methods:**

This is a two-arm, prospectively registered, randomized trial with concealed allocation, double-blind, and intention-to-treat analysis. Forty-four patients with HFrEF will be recruited. The experimental group will undertake 25–30 min aerobic exercise training associated with tDCS, for 4 weeks. The control group will undergo the same aerobic exercise training, but with sham-tDCS. The primary outcome will be functional performance by the 6-min walk test. Secondary outcomes will include cardiopulmonary exercise capacity, inflammatory cytokines, and quality of life. Outcomes will be collected by a researcher blinded to group allocation at baseline (T0) and after 4 weeks of intervention (T1).

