## Methods

### Study design

The ELETRIC study is designed to investigate the effects of noninvasive brain stimulation in patients with HF (*Eletroestimulação em Insuficiência Cardíaca*, in Portuguese).

A clinical, randomized parallel-design 1:1 ratio allocation, controlled, blinded assessors, participants and therapists, and intention-to-treat analysis will be carried out by the Federal University of Amazonas (Universidade Federal do Amazonas) at the University Hospital Getúlio Vargas, in the city of Manaus, North Brazil (Fig. 2). The study was approved by the ethics committee (CAAE 64652122.0.0000.5020) and registered by ReBEC (Brazilian Registry of Clinical Trials), registry RBR-10w787j6. The study protocol adheres to the SPIRIT 2013 recommendations.

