### Secondary outcome measurements

Secondary outcomes are cardiopulmonary exercise capacity (CPX), inflammatory cytokines, and quality of life.

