### Intervention

Clinical assessments will be performed at baseline (T0) and at the end of 4 weeks (T1), consisting of a symptom-limited cardiopulmonary test, 6MWT, quality of life assessment, and laboratory tests (Table 1).

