### Criteria for discontinuation

The criteria for discontinuation are worsening of symptoms, clinical instability, and emergence of serious infectious or viral diseases that are difficult to control.

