### Statistical analysis

Exploratory analyses will be carried out allowing a survey of the frequency distribution and calculation of means and standard deviations. The 95% confidence intervals will be considered, and effect sizes will be calculated for primary and secondary outcomes. Statistical significance will be stipulated with *p*<0.05. The Shapiro-Wilk test will be applied to analyze the normality of the sample distribution; unpaired *t*-test will be used for numeric variables, comparing means between two groups; and Fisher’s exact test will be used for categorical variables. Two-way ANOVA for between factors accompanied by post hoc Bonferroni analysis will be used to measure and predict the degree of relationship between inter- and intragroup variables. Pearson correlation will be performed to test the association between two continuous variables, and multiple linear regression will be used to quantify the relationship between predictor variables and the outcome variable. For data analysis, the statistical programs Jamovi (Jamovi Project, Sydney, Australia) and GraphPad Prism 7.0 (GraphPad, CA, USA) will be used. We will not perform sub-analysis, mainly because the primary stage is well defined in relation to the central question. Furthermore, it may be necessary to perform adjusted calculations for some variables, such as age, weight, BMI, EF%, and β-blocker drug dose. For this purpose, the utilization of these variables as covariates will be used in the ANOVA two-way analysis described above.

Participants who discontinue or deviate from intervention protocols will have their data on 6MWT and inflammatory cytokines collected.

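### The follow-up rule for participants who stop or deviate names 6MWT and cytokines but not CPX or MLHFQ, and does not match the unrestricted intention-to-treat statement

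*Protocol article*

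**What the plan says.** All references are to the protocol article.

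- **Analysis principle.** The abstract describes a "randomized trial with concealed allocation, double-blind, and intention-to-treat analysis". Study design repeats it: "blinded assessors, participants and therapists, and intention-to-treat analysis will be carried out". Neither place confines the principle to the primary outcome.
- **Outcomes.** The primary outcome is 6MWT distance. For the rest: "Secondary outcomes are cardiopulmonary exercise capacity (CPX), inflammatory cytokines, and quality of life".
- **Schedule.** The Intervention section sets assessments at baseline (T0) and 4 weeks (T1), "consisting of a symptom-limited cardiopulmonary test, 6MWT, quality of life assessment, and laboratory tests".
- **After stopping or deviating.** One sentence, at the end of Statistical analysis, deals with this group: "Participants who discontinue or deviate from intervention protocols will have their data on 6MWT and inflammatory cytokines collected".
- **Reasons for stopping.** The Criteria for discontinuation section lists "worsening of symptoms, clinical instability, and emergence of serious infectious or viral diseases".

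**The concern.** The sentence on participants who stop or deviate covers two of the four outcome domains. The two it leaves out, CPX (peak VO2, VE/VCO2 slope, OUES) and MLHFQ, are the subject of two of the three secondary objectives. Site staff who follow the text would obtain a walk test and a blood sample at T1 and need do no more.

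The listed reasons for stopping bear directly on exercise capacity and quality of life, so the missing values would probably not be a random subset. The CPX and MLHFQ comparisons could then describe participants who stayed on treatment and stayed stable, while 6MWT and cytokines describe everyone, all under one intention-to-treat label. Randomisation would no longer fully protect the first two comparisons.

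This is not a complaint that a missing-data method is absent, which an analysis plan may supply. It concerns a rule on what is collected. A later analysis plan cannot recover T1 values that were never taken.

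**Working it through.** **Step 1. Set the statements side by side.**

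| Outcome | Role | Scheduled at T1 (Intervention) | Named for those who stop or deviate (Statistical analysis) |
|---|---|---|---|
| 6MWT | primary | yes | yes |
| Cytokines | secondary | yes (laboratory tests) | yes |
| CPX | secondary | yes | no |
| MLHFQ | secondary | yes | no |

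The Intervention section does not say whether its schedule continues after treatment stops. No other section says that CPX or MLHFQ will be obtained from this group.

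**Step 2. Look for a figure in the plan.** The article gives no rate of discontinuation or deviation. The 20% in the Sample size section is an allowance for sample loss in the 6MWT calculation. Participants covered by the follow-up sentence still have their 6MWT measured, so they are not the group that this 20% describes. It cannot be used to count who would lack CPX and MLHFQ.

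**Step 3. Illustrate the size under stated assumptions.** Let q be the proportion of an arm that stops or deviates, and let g be the amount, in SD units, by which those participants are worse than completers, taken as equal in the two arms. The mean over all randomised participants in an arm lies q × g below the completer mean. Omitting these participants therefore shifts the between-arm difference by

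bias = (q in one arm − q in the other) × g.

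All values of q and g below are assumptions.

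| Stopping, arm v arm | g = 0.5 SD | g = 1.0 SD |
|---|---|---|
| 20% v 20% | (0.20 − 0.20) × 0.5 = 0 | (0.20 − 0.20) × 1.0 = 0 |
| 25% v 15% | 0.10 × 0.5 = 0.05 SD | 0.10 × 1.0 = 0.10 SD |
| 30% v 10% | 0.20 × 0.5 = 0.10 SD | 0.20 × 1.0 = 0.20 SD |

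The sign depends on which arm stops more. More stopping under active tDCS makes the completer comparison too favourable to it; more stopping under sham does the reverse.

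The article plans no effect size for CPX or MLHFQ. Its Cohen's f of 0.41 belongs to 6MWT and is not a yardstick for these figures.

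**The case against.** **The sentence may be a minimum, not a limit.** It does not say that only these two outcomes are collected, and the T0/T1 schedule is not restricted to completers. This stands as far as it goes: exclusion of CPX and MLHFQ is an inference. It is still the natural reading, because singling out two of four domains has little purpose if all four are meant.

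**A reader might infer that the CPX and MLHFQ analyses are per-protocol, and that the planned ANOVA is bound to drop these participants.** The documents do not support that. No section selects participants for analysis by adherence, and the article states no rule for missing values. A complete-case comparison among adherent participants is the likely result of not collecting the data, but it is not a declared analysis set.

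**A reader might infer that a few missed sessions trigger the rule.** Deviation is not defined, and the retention section lets absences be made up within the same week. The text does not settle this.

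**A reader might infer that about 9 of 44 participants (20%) would be missing, or that a bias is established.** Neither follows. The 20% describes a different group, and nothing suggests that stopping will differ by arm: both arms have the same exercise programme under blinding. With equal stopping and an equal deficit the bias is zero.

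**CPX may not be obtainable in symptomatic participants.** CPX is a symptom-limited test, so some outcome-related gaps may remain whatever the sentence says. That stands, and it is why the remedy for CPX is to reconcile the text. It does not apply to a questionnaire.

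**Conclusion.** The point holds as an inconsistency within the article on two secondary outcomes. The follow-up rule, on its natural reading, does not deliver the data that the unrestricted intention-to-treat statement needs for CPX and MLHFQ. The likely consequence is a complete-case comparison of adherent participants for those two outcomes, with missingness related to prognosis.

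The size is unknown from the documents. The illustrated range is 0 to 0.20 SD. It rests on assumed stopping rates and an assumed deficit common to both arms, and it needs unequal stopping to be above zero. The primary 6MWT comparison and the cytokines are explicitly covered after discontinuation, so the main conclusion of the trial is not at risk from this sentence. It should be corrected while T1 data can still be collected.

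**What to change.** **MLHFQ.** Amend the sentence in Statistical analysis so that MLHFQ is also collected at T1 from all randomised participants, whatever their adherence, at the visit already held for 6MWT and cytokines. Analyse it by randomised arm. The cost is a protocol wording change and one 21-item questionnaire per affected participant.

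**CPX.** Reconcile Study design, Intervention and Statistical analysis in one of two ways:

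- state that CPX at T1 is sought from all randomised participants, and report the reason for each missing value by arm; or
- state that the CPX comparison is not intention-to-treat, and describe whom it covers.

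The first option adds tests in some participants and may still leave gaps. The second costs only wording but gives up the intention-to-treat claim for CPX. When testing is clinically appropriate is for the investigators to decide and is not part of this point.

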### Data monitoring

Details of clinical site monitoring are documented in a Research Ethics Committee-approved clinical monitoring plan, which describes in detail who will perform monitoring, how often, and the distribution of monitoring reports.

An interim analysis and stopping committee were established at the request of the research ethics committee. This committee will meet regularly (every 3 months) to review the data and assess the study’s continuation. Nonetheless, any unforeseen adverse events that transpire during the intervention period will be promptly reported to a highly skilled physiotherapist who is not directly engaged in the trial’s execution. This physiotherapist will be accessible to make the ultimate decision to halt the trials in the event of unexpected harm.

All events must be managed and reported in compliance with all applicable regulations and included in the final clinical trial report. All physical/clinical symptoms described at each visit will be recorded as an adverse event if they occur or worsen during the study and are related to the study protocol.

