#### Cardiopulmonary exercise test

Physical capacity will be assessed by CPX on a CG-04 ergometric bicycle (Inbramed, Porto Alegre, Brazil) with data directed to the breath-to-breath ergospirometer (PNOE, ENDO Medical, CA, USA) with a ramp protocol of 5–10 watts per minute. The volunteer must use a mask and mouthpiece system in which there is a bidirectional digital volume transducer, that is very light and precise, and capable of measuring lung volumes. The subjects will be familiarized with the exercise bike and with the Borg CR10 scale. Volunteers will be encouraged to perform the test until exhaustion. The test will be carried out together with a cardiologist medical professional, so that it is possible to detect any cardiac arrhythmias as well as assistance in the event of any intercurrences and a trained physiotherapist. The protocol will consist of the following phases: (I) rest period of 5 min sitting on the bicycle, (II) warm-up with free load for 3 min, (III) incremental phase in the ramp protocol with a cadence of 60 rotations per minute, (IV) 1-min active recovery with free load, and (V) passive recovery of 5 min standing on the bicycle. A 12-lead electrocardiogram (ECG) will be continuously monitored during the test, and blood pressure will also be recorded before the test, every 3 min during exercise and in the recovery period. The Borg CR-10 dyspnea scale will also be used to assess muscle fatigue in the lower limbs and shortness of breath during the test. The test will be interrupted if the patient presents physical exhaustion and/or presents one or more of the following criteria: (I) maximum/leg fatigue or dyspnea; (II) angina or electrocardiographic evidence of ischemia or malignant arrhythmia (ventricular tachyarrhythmia, bigeminy, and [atrioventricular and branch] blocks); (III) pressure changes with an increase greater than 220 mmHg in systole and above 100 mmHg in diastole; (IV) SpO_2_ drops to values ≤ 88%; and (V) patient request interruption of the test. Subjects will be encouraged to reach the maximum capacity limited by symptoms, characterized by a *V̇*CO_2_/*V̇*O_2_ ratio (RER) ≥ 1.1. The metabolic variables will be measured by the PNOE ergospirometer (ENDO Medical, CA, USA), and the gas analysis for the primary outcome will measure the absolute peak *V̇*O_2_ (mL/min), the corrected peak *V̇*O_2_ (mL/kg/min) and production of carbon dioxide (*V̇*CO_2_, mL/min). The variables slope of minute ventilation by CO_2_ exhalation (*V̇*E/*V̇*CO_2_ slope) and O_2_ consumption efficiency (OUES) will be evaluated during the cardiopulmonary test and before and after aerobic training. For variable calculations, the *V̇*E/*V̇*CO_2_ slope will be obtained by linear regression analysis of the relationship between *V̇*E and *V̇*CO_2_. Additionally, the relationship between *V̇*O_2_ and *V̇*E, expressed by the efficiency of oxygen consumption (OUES), will be determined by the logarithmic curve using the following equation: *V̇*O_2_ =a*log *V̇*E + b, where the constant “a” represents the rate of increase of V̇O2 in response to *V̇*E increment (Myers et al., [22]).

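### The adverse-event rule records a symptom only if it is related to the study protocol, which conflicts with the sentence before it and may leave symptoms attributed to heart failure out of the adverse-event counts

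*Protocol article*

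**What the plan says.** The rule is the last sentence of Data monitoring in the protocol article. It takes "All physical/clinical symptoms described at each visit" and says that these "will be recorded as an adverse event if they occur or worsen during the study and are related to the study protocol". Two conditions are joined: the symptom must be new or worse, and it must be related to the protocol. The article does not say who judges relatedness, when, or by what criteria.

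The sentence directly before it reads: "All events must be managed and reported in compliance with all applicable regulations and included in the final clinical trial report". It carries no relatedness condition, and the word events is not defined there.

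The same section sets up two safety routes. A committee "will meet regularly (every 3 months) to review the data". Separately, "any unforeseen adverse events that transpire during the intervention period will be promptly reported to a highly skilled physiotherapist", a person outside the conduct of the trial who can decide to halt it. The second route depends on something counting as an adverse event.

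Other sections bear on the point:
- Criteria for discontinuation lists worsening symptoms and clinical instability, whatever their cause.
- Cardiopulmonary exercise test has a cardiologist present, "so that it is possible to detect any cardiac arrhythmias".
- Intervention states that participants, evaluators and those applying the protocols are blinded.

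**The concern.** An adverse event is usually recorded first and its cause graded second. Here the causal judgement decides whether the record exists.

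That order matters in this population. Eligible patients are in NYHA class II or III with an ejection fraction below 40%, and the Background names exercise intolerance and chronic fatigue among the main symptoms of the disease. A new or worse symptom of that kind is easily put down to heart failure. Under the rule as written it is then not an adverse event.

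It also matters for the design. Both arms do the same exercise and differ only in active versus sham stimulation. The strength of that design for safety is that cause can be read from total events by arm, without an opinion on each case. Screening on opinion first gives part of that strength away. The article describes the combination as the first of its kind in these patients, so there is little experience on which to base such an opinion.

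**Working it through.** No figure in the article bears on this point, so the check is a reading of the text plus a short piece of algebra.

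**1. What the rule does to each kind of symptom.**

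| New or worse during the study? | Judged related to the protocol? | Recorded as an adverse event? |
|---|---|---|
| Yes | Yes | Yes |
| Yes | No | No |
| No | Either | No |

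The second row is the problem.

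**2. Whether the preceding sentence repairs it.** There are two ways to read the requirement to report all events.
- *Events means adverse events as the next sentence defines them.* The final report then holds related symptoms only, and the second row is lost from it.
- *Events means everything that happens.* The final report must then contain symptoms that the recording rule does not require anyone to record as adverse events. The two sentences conflict, and site staff cannot tell which to follow.

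Both readings call for a change of wording.

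**3. Whether the prompt-report route repairs it.** It is triggered by unforeseen adverse events. A symptom in the second row is not an adverse event under the rule, so it does not clearly trigger the route.

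**4. Whether the discontinuation criteria repair it.** The text is "The criteria for discontinuation are worsening of symptoms, clinical instability, and emergence of serious infectious or viral diseases". It has no relatedness condition, so some deterioration would leave a trace. But it reaches only patients who stop, and it is not an adverse-event record.

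**5. What the filter does to a comparison of arms.** Let *b* be the expected number of new or worsening symptoms in the sham arm and *b + d* the number in the active arm, so that *d* is the excess due to stimulation. Let *p* be the share judged related. Assume that *p* is the same in both arms, since staff are blinded.
- All events: (*b + d*) − *b* = *d*.
- Recorded events only: *p*(*b + d*) − *pb* = *pd*.

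The article gives no value for *p*, which may lie anywhere from 0 to 1. At *p* = 1 nothing is lost. At any smaller value the visible excess shrinks in proportion and rests on fewer events. Equal *p* creates no excess where none exists, so the filter weakens the comparison without tilting it.

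**6. Whether relatedness can be judged well.** A blinded assessor does not know whether the current was active. That person can say whether a symptom followed a session, but cannot reliably say whether stimulation caused it. The contrast between arms answers that question, and it needs all the events.

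**The case against.** The strongest reply is that the article never says unrelated events are discarded. The sentence on reporting all events stands next to the rule and has no relatedness condition. This stands as far as it goes: the text shows an unresolved tension, not a settled exclusion from the report.

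Several stronger readings are tempting, and the document does not support them.
- A reader might infer that unrelated events never reach the stopping committee. The committee reviews data whose content is not specified, and nothing limits it to related events.
- A reader might infer that the treating team decides causality. The article names no judge.
- A reader might infer that a planned harm analysis is spoiled. No safety outcome or between-arm harm analysis is described, and in a condensed article that silence is no fault. What is weakened is a comparison that could be made.
- A reader might extend the rule to arrhythmias and hospital admissions. It names symptoms described at visits. Rhythm is watched for separately in the exercise test, and admissions are not mentioned in the rule.
- A reader might size the flaw from the arm of 22, where one event is 1/22 = 4.5%. That reflects the arm size and says nothing about how many events would be lost.

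Two further points are fair. Relatedness to the protocol is wider than relatedness to stimulation, so symptoms provoked by training or testing could qualify. Changes of drug or dose are also to be recorded, so serious deterioration would probably show somewhere. Neither removes the condition from the rule.

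**Conclusion.** The point holds as a defect in a stated rule. Relatedness is a condition of recording a symptom as an adverse event, and this does not fit the sentence before it. Symptoms judged to be due to heart failure may be missing from the adverse-event counts and from the prompt-report route.

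The wording defect is certain. The consequence is a possibility whose size the article does not allow one to estimate. It rests on two assumptions: that staff apply the sentence as written, and that the full protocol or the case report form does not override it. With staff blinded, there is no reason to expect the loss to favour either arm. The primary analysis of walking distance is not affected. A statement at the end that adding stimulation was safe would be weaker than the design could support. The change is worth making early, because symptoms not written down at the time may not be recoverable.

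**What to change.** In Data monitoring:
1. Delete the closing relatedness condition from the recording rule.
2. Record every symptom or clinical event that occurs or worsens during the study, whatever its cause. Count from consent, so that baseline testing is covered. The note to Table 1 places baseline assessment before randomisation, so a rule starting at randomisation would be narrower than the present text and would miss events during the first exercise tests.
3. Grade seriousness and relatedness as separate fields, by assessors who remain blinded.
4. Tabulate all events by arm for the committee and the final report, with related events as a subset.
5. Use one defined term for events in both sentences and in the prompt-report route.

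The cost is a few more lines on the visit form and a longer list of low-grade events. The change concerns recording only and leaves treatment, testing and the discontinuation criteria as they are.
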